# 1 Summary

## **PROTOCOL IDENTITY AND AIM**

Protocol title: IPISTOSS

Aim of study: To determine if skin-to-skin contact results in a better physiological stabilization, altered epigenetic profile and better long-term neurodevelopmental outcome.

## **INTERVENTION**

Skin-to-skin contact with a parent from birth

## **METHODS**

Study design: randomized controlled trial.

Duration: Continuous skin-to-skin contact with any parent during the first six hours of life, and as much as possible the first three days.

Primary hypothesis: Does cardiorespiratory stabilization improve?

Effectiveness outcomes: all other outcomes.

Safety parameters: respiration, thermal control, infections.

## **STUDY POPULATION**

Study subjects: Infants born with gestation between 28+0-and 32+6 weeks at Karolinska University Hospital (Danderyd, Huddinge and Solna) in Stockholm, or at Stavanger University Hospital in Stavanger

Number: 150

## **TIME FRAME**

First subject enrolled: 20170501

Last subject enrolled: 20201031

Last subject completed follow-up: 20230131

## 2 ABBREVIATIONS

| Abbreviation | Explanation                                                  |
|--------------|--------------------------------------------------------------|
| AE           | Adverse Event                                                |
| APIB         | Assessment of Preterm Infants' Behavior                      |
| SAE          | Serious Adverse Event                                        |
| ASQ          | Ages and Stages Questionnaire                                |
| BSES         | Breastfeeding Self Efficacy Scale                            |
| CMM          | Centrum för Molekylärmedicin (Centre for Molecular Medicine) |
| CPAP         | Continuous Positive Airway Pressure                          |
| CRF          | Case Report Form                                             |
| EEG          | Electroencephalography                                       |
| EPDS         | Edinburgh Postnatal Depression Scale                         |
| HRV          | Heart Rate Variability                                       |
| IBFAT        | Infant Breastfeeding Assessment Tool                         |
| IBS          | Index of Breastfeeding Status                                |
| IBQ          | Infant Behaviour Questionnaire                               |
| KMC          | Kangaroo Mother Care                                         |
| KTA          | Karolinska Trial Alliance                                    |
| MCHAT        | Modified Checklist for Autism in Toddlers                    |
| PCERA        | Parent-Child Early Relational Assessment Scale               |
| PKU          | Phenylketonuria (and term for metabolic screen)              |
| RCT          | Randomized Controlled Trial                                  |
| SCRIP        | Stability of the CardioRespiratory system In the Preterm     |
| SOP          | Standard Operating Procedure                                 |
| SPSQ         | Swedish Parenthood Stress Questionnaire                      |
| SSC          | Skin-to-Skin Contact                                         |
| STAI         | The Spielberg State-Trait Anxiety Inventory                  |
| SUPC         | Sudden Unexpected Postnatal Collapse                         |
| WHO          | World Health Organization                                    |

### 4 BACKGROUND

#### 4.1 Condition

Infants born very preterm are cared for in the neonatal ward in their first weeks and months of life. Being born too soon means that those organs that would have developed in the uterus must instead do so in the hospital environment. This requires many aspects, including support for breathing, enteral and parenteral nutrition, humidity and warmth, monitoring, gentle supportive care and proximity to parents. The first few hours of life are especially important, during which transition to extrauterine life takes place, the infant's breathing and circulation changes from reliance on the lungs rather than the placenta. Events taking place in these first few days and weeks do impact future health and family relationships. The consequences of prematurity can result in symptoms from many organs in the short and long term, but above all long-term brain development can be adversely affected, with psychomotor impairments (1).

Current practice is to care for premature infants in incubators. The incubator provides needed humidity and warmth, but it also results in abrupt separation from mother. Empirically, it is observed that premature infants and

their parents benefit from intermittent skin-to-skin contact during the stay in the neonatal wards. For full term newborns it is well established that skin-to-skin contact is beneficial (2). For preterms, initiation of skin-to-skin contact and the number of hours per day it is provided depends on infants gestational age and medical condition as well as the circumstances of the ward and the parents.

In Swedish the term "*hud-mot-hudkontakt*" is the direct translation of "skin-to-skin contact" (SSC). The term "Kangaroo Mother Care" (KMC) is often used as a synonym, however the definition of KMC is a broader concept including support for breastfeeding and early discharge from hospital.

## 4.2 Intervention

### Intervention:

The intervention in this study is the place of care, the exact same care is given but in SSC with a parent or surrogate instead of resuscitator or incubator. This will be continuous for the first six hours of life, and as much as possible during the first 72 hours.

### Previous studies:

In a recently updated Cochrane-review a 40% lower mortality is reported at term equivalent age in infants born below 2kg cared for in SSC/KMC compared to conventional care (3,2% vs 5,3%; RR 0,60, 95% CI 0,39-0,92; 8 studies, 1239 infants), a shorter hospital stay, and higher prevalence duration and degree of breastfeeding (3). In almost all these studies, KMC was initiated when the infant was stable. The median age of initiation was 3,2 to 24,5 days, only in one study was KMC initiated around 10 hours (4). The implication is that two thirds of deaths among preterm infants would have occurred before the time any infant could have been assessed as stable enough for KMC (5).

Two studies from middle income countries report on SSC and physiological stabilization. One RCT from South Africa enrolled infants with birthweight 1200-2199 g, in the first 6 hours of life: those in SSC had 100% stability scores compared to 46% for those in incubators. Those in incubators also had significantly lower temperatures (6). In a similar study from Vietnam infants with birthweight between 1500-2500 g in the SSC group had significantly improved scores for transition to extrauterine life. Further, they required less respiratory support, intravenous fluids and antibiotics during hospital stay (7).

This current study is ongoing since May 2017 in Stavanger, Norway, and since November 2018 at Karolinska University Hospital in Huddinge, Stockholm, Sweden.

### Risks of the intervention.

The main risk factor for immature and unstable infants during SSC is obstructive apnoea, from a position failing to ensure patent airway. To avoid this all infants will be positioned correctly, and during transfer or transport we will ensure fixation on parent or surrogate with a garment. All infants will be monitored ongoing with pulse oximetry. Preterm and low birth weight infants are susceptible to hypothermia if the environment is too cold. They should therefore be covered with a blanket when receiving SSC. A consequence of this is that staff may have difficulty to visually assess the condition of the infant as is possible in open or closed incubator. Therefore, staff will make regular observation of the infant in the SSC position, as they would for incubator infants. There is further a risk that the interpretation of the infant's condition is misinterpreted, as unstable infants were not previously in SSC.

### Benefits of the intervention.

Benefits of the study could be that the early SSC enhances the physiological transition from intrauterine to extrauterine life and protects against some of the medical problems associated with preterm birth. Another benefit could be a reduced time of separation allowing parents greater opportunity to bond to their infants.

## 4.3 Aim of the study

The context for this study is the global health situation for preterm and low birth weight infants. Most of these are born in developing countries and have a high mortality rate. The high technology care provided in developed countries is seen as a standard of care, even though it can seldom be provided due to lack of resources. Healthy full-term infants are often traditionally cared for with the mother from the beginning, and often in SSC. Should the infant be born preterm, or by caesarean section, or be sick in any way it is admitted to neonatal wards that are generally already full of sick infants. Mothers have limited access to their infants and are usually only allowed in at feeding times. The numbers of infants in relation to staff and space contributes to morbidity and mortality that could have been prevented with relatively simple measures (8). In many parts of the world there are KMC wards established for more mature and stable infants for ongoing SSC as support for breastfeeding and weight gain while awaiting discharge. WHO recommends that all stable low birth weight infants to be kept in SSC (9). A study is currently underway in low- and middle-income countries looking at survival rates from immediate SSC (Immediate KMC Study) under the sponsorship of the WHO.

In Sweden intermittent SSC is used in neonatal intensive care units and small infants are seen to do well. There is however very little research on immediate SSC on infants born below 33 weeks gestational age. We wish to study what happens if an earlier start of this simple and inexpensive intervention is introduced. The study population will be infants born between gestational age 28+0 to 32+6 weeks, approximating 1-2 kilograms in weight. The aim is to conduct a study in a high-income country context to elucidate more advanced effects and underlying mechanisms as well as the safety of the method in a manner that is not possible in low income countries with scarce resources. This study therefore complements the abovementioned WHO study on survival.

## 5 HYPOTHESES

### 5.1 Primary hypothesis

Does skin-to-skin contact during the first six hours lead to improved cardiorespiratory stabilization?

### 5.2 Secondary hypotheses

The secondary hypotheses will examine whether SSC leads to differences in:

- Respiratory function (need for respiratory support, surfactant, time on ventilator, CPAP and extra oxygen use)
- Heart Rate Variability (HRV)
- Thermal regulation
- Infections
- Breastfeeding, nutrition and growth
- Epigenetic profile after birth and later in development
- Microbiome
- Brain maturation, EEG
- Structural maturation of brain on MRI
- Attachment and interaction between parents and infants

- Brain functions in areas reflecting sensitive parenting (fMRI)
- Parents' experiences and mental health
- Capacity in infants and mothers to regulate stress and interaction
- Psychomotor development (neurology, motor function, cognition, behaviour, language)

## 6 ENDPOINTS

### 6.1 Primary endpoints

Cardiorespiratory stability is measured with the SCRIP score (Stability of the CardioRespiratory system In the Preterm), a scale that summates the respiratory (respiratory rate, oxygen saturation, need for respiratory support) and circulatory (pulse) variables in the infant (7). Observations are made during a five-minute period every 15 or 30 minutes during the first six hours, according to prepared template. For each five-minute period the recorded parameters are used to calculate a summary score of physiological stability.

### 6.2 Secondary endpoints

The time points below are the *corrected age* of the infant, calculated from expected date of full-term birth (not the chronological age calculated from actual date of premature birth). For some secondary outcomes only a subsample of infants will be studied.

Respiratory function: Need for surfactant, number of days in ventilator, number of days in CPAP, number of days requiring oxygen.

Heart rate variability: Postpartum, after 48-72 hours, at discharge and at 3-4 months.

Thermal regulation: Axillary temperature is measured continuously, alternatively every hour on infant, and if in SSC also on parent.

Infections: Proportion of infants that experience sepsis during admission in the neonatal ward according to case record, and total number of days treated with antibiotics.

Breastfeeding, nutrition, and growth: Age at first feed, age at first passage of meconium, time to full enteral feeding, time to weaning from feeding tube, lowest weight, time to return to birth weight, weight gain in grams per day during admission, and weight at discharge as well as term age as per case record. Nutrition and breastfeeding status will be completed weekly according to the Index of Breastfeeding Status (IBS) questionnaire during hospital stay, at discharge, at term age, at 3-4 months of age and at 12 months. The Breastfeeding Self-Efficacy Questionnaire (BSES) will be completed at 7 days, 3-4 months, and the Infant Breastfeeding Assessment Tool (IBFAT) each week during admission, at discharge, at term age and at 3-4 months.

Epigenetics: Whole genome analysis as well as locus specific methylation of stress related genes for Oxytocin receptor (OXTR), glucocorticoid receptor (NR3C1), Arginine-vasopressin receptor (AVP), Proopiomelanocortin (POMC), Glutamate decarboxylase-1 (GAD1), Glutamate receptor (GRM1), Brain-Derived Neurotrophic Factor- (BDNF), serotonin transporter (SLC6A4 och SERT), serotonin receptor (5H2A) och serotonin degradation enzyme (MAOA) in cord blood postpartum, in buccal swabs postpartum and at 6 hours, whole blood from opportune time during first 6 hours, whole blood and buccal swabs at 48-72 hours, at 3-4 months and at 24 months of age.

Microbiota: Infant colonization by microbiome (bacteria) is identified by DNA analysis from fecal samples at 0-6 hours, 72 hours, 3-4 months, 12 och 24 months, and compared to the parents. Vaginal, rectal, and skin samples from mother and partner are collected at 0-6 hours.

Functional maturation of brain: EEG-activity at 4-10 days of age and at term age.

Structural maturation of brain: MR brain at term age.

Attachment: Attachment as assessed by video filming at 3-4 months of age in conjunction to the "Still Face-test", as well as interaction as interpreted by the Parent-Child Early Relational Assessment Scale (PCERA), which will also be done at 12 and 24 months of age.

Brain function: Functional magnetic resonance imaging (MRI) to demonstrate activation patterns in specific areas in maternal brain when she studies pictures of her own and other children in different emotional states, when her infant is 3-4 months old.

Parental mental health: Experience of care as assessed by interview at discharge. Further according to Edinburgh Postnatal Depression Scale (EPDS) at 7 days, 3-4 months and 12 months of infant age, the Spielberg State-Trait Anxiety Inventory (STAI) at 7 days, 3-4 months and 12 months of infant age and the Swedish Parenthood Stress Questionnaire (SPSQ) at term age, 3-4 months and 12 months of infant age.

Stress reactivity: According to salivary cortisol levels in infant and mother on the morning and evening near day of hospital discharge, and in the same day before and after nappy change (stressor), at 3-4 months of age, and the same day as the Still Face-test (stressor), and at 12 months of age.

Infant psychomotor development: as recorded in hospital case record at term age, and again at 3-4 months, 12 months and 24 month of age, further according to Assessment of Preterm Infant Behaviour (APIB) at term age, according to Infant Behaviour Questionnaire (IBQ) and Ages and Stages Questionnaire (ASQ) at 3-4 months (ASQ 3-8) and 12 months (ASQ 9-14)as well as developmental assessment according to Bayley Scales of Infant and Toddler Development 3rd Edition, and Modified Checklist for Autism in Toddlers (MCHAT) at 24 months age.

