## 7 METHODS

### 7.1 Method overview

This is a prospective multicenter randomized controlled trial. Screening for study subjects takes place among women with threatening premature birth in the antenatal and labor ward, with randomization taking place antenatally. The study population is 150 infants (75 infants in control and in intervention) born between gestational age 28+0 and 32+6 weeks at Karolinska University Hospital labour wards in Danderyd and Huddinge in Stockholm and at Stavanger Universityhospital in Norway. The intervention is skin-to-skin contact with either parent or with a surrogate chosen by them, the SSC should be uninterrupted during the first six hours of life, and as much as possible in the first 72 hours. Data will be collected during this time, and then during the period of admission, and continued until the infant reaches 24 months corrected age (described further below). Certain selected outcomes will be studied in subsamples of the 150 subjects, and for practical reasons some at only one site. Some families studied may later be transferred elsewhere in the country, data for these will continue to be collected as far as possible. There may also be certain exclusions due to language and interpreter problems that may influence data. Discussion on sample sizes for subsamples is ongoing.

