### As soon as possible after birth:

- Cord blood and buccal swab is taken from the infant for epigenetic testing.
- Fecal sample and skin swab taken from the infant for analysis of microbiota
- Maternal samples from rectum, vagina and skin for microbiota analysis.
- Father or partner swabbed for microbiota analysis.
- HRV

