(MAOA) i cord blood postpartum, in buccal swabs postpartum. Midwife or nurse in labour ward collect cord blood concomitant with routine collection. Neonatal nurse collects blood samples at the same time as required clinically, as well as buccal swab during hospital stay or at follow-up visit. Samples are transported to the Unit for "Medicinsk Epigenetik, Centrum för Molekylärmedicin", KI. Analysis is undertaken by responsible researcher.

Microbiota: Infant microbiome colonization is identified with DNA analysis from fecal samples and skin swabs, and compared to that of their parents. Samples from infant are collected by ward nurse. Tests from parents are collected by nurse, or by the parents themselves. Samples are sent to the Center for Translational Microbiome Research (Molekylär- och Tumörbiologiskt Centrum; MTC).

Brain function maturation: EEG is measured with 8 leads using existing apparatus in clinical use. The results will be interpreted by the Nurture Science Programme, Columbia University, NY.

Structural maturation of brain: MR brain will be done on a subsample at term age. Results will be interpreted by radiologists.

Attachment: attachment will be assessed by psychologist on films made during the "Still Face-test" as well as the Parent-Child Early Relational Assessment Scale (PCERA). Filming is done by research staff. A psychologist or other appropriately trained staff at Linköping University or Karolinska Institutet will interpret the films.

Brain function: Functional magnetic resonance imaging (fMRI) will examine activation patterns in specific areas on mother's brain while she looks at pictures of her own and other infants in different moods. Parents will be invited to radiology department and the examination conducted by radiologists who will assess whether there are any structural differences, with the hypothesis that functional and structural connectivity in parenting behavior specific areas (e.g. prefrontal cortex and amygdala) are related to time in SSC.

Parental mental health: Experience of care will be assessed in interviews at discharge. Questionnaires Edinburgh Postnatal Depression Scale (EPDS), The Spielberg State-Trait Anxiety Inventory (STAI) and the Swedish Parenthood Stress Questionnaire (SPSQ) are administered. A research nurse distributes the questionnaires and parents complete them during hospital stay or at home before follow-up visit. Proportions are analyzed.

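### The parental skin swab is not timed against first skin contact, so one reference for infant colonisation may be post-contact in the SSC arm but generally not in the control arm

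*Protocol*

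**What the plan says.** Section 5.2 of the protocol lists the microbiome among the secondary hypotheses. Section 6.2 defines the endpoint on infant "fecal samples at 0-6 hours, 72 hours, 3-4 months, 12 och 24 months, and compared to the parents", and sets the parental sampling in the next sentence: "Vaginal, rectal, and skin samples from mother and partner are collected at 0-6 hours".

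Section 7.2 puts the parental sampling under the heading "As soon as possible after birth". The items there are "Maternal samples from rectum, vagina and skin for microbiota analysis" and "Father or partner swabbed for microbiota analysis", in the same list as the infant's first fecal sample and skin swab. Section 9.1 brings infant skin into the comparison as well: "Infant microbiome colonization is identified with DNA analysis from fecal samples and skin swabs, and compared to that of their parents". Neither 6.2 nor 7.2 lists a later parental sample.

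The Summary gives the intervention as "Skin-to-skin contact with a parent from birth". Section 7.1 describes it as "skin-to-skin contact with either parent or with a surrogate chosen by them", without a break until six hours of age. Section 8.1 requires a provider who can start within the first hour, and section 8.3 accepts that the start will sometimes be delayed.

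**The concern.** A reference sample should be taken under the same conditions in both arms, and before the treatment can alter it. Here the treatment is contact with the skin of the person who may be swabbed, and the sampling window coincides with the treatment period.

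If a parent's skin is swabbed after the infant has lain on it, the swab can carry flora from the infant. Infant and parent then look more alike even if the infant has acquired nothing from the parent. This is the direction in which a real effect of SSC on colonisation would appear. As no later parental sample is listed, the same swab would serve as the skin reference at every later infant time point too.

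**Working it through.** The plan gives no figure on this point, so the check sets the timings side by side.

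1. **Sampling window.** Section 6.2 allows 0 to 6 hours. Section 7.2 asks for prompt sampling after birth, with no clock limit and no order relative to SSC.
2. **Contact period in the SSC arm.** It is planned from birth (Summary) to 6 hours (sections 4.2, 7.1 and 7.2). The provider must be able to start by 1 hour (section 8.1).
3. **Overlap under section 6.2.** With a start at birth, 6 − 0 = 6 hours. With a start at 1 hour, 6 − 1 = 5 hours. So 5/6 (83%) to 6/6 (100%) of the window falls after the start of contact. This is a share of permitted time, not of swabs. A delayed start under section 8.3 would shrink it.
4. **Under section 7.2.** Swab and contact are both tied to birth and neither is placed first. A prompt swab may precede contact, but it also complies if it follows.
5. **Control arm.** The infant receives conventional care over these hours. Section 8.3 lets parents depart from the allocation after individual assessment, so contact before the swab is possible but should be unusual.
6. **What the order can affect:**

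| Comparison | Affected by the order of swab and contact? |
|---|---|
| Infant against skin swab of the parent giving SSC | Yes, in the SSC arm |
| Infant against skin swab of a parent not giving SSC | No |
| Infant against vaginal or rectal samples | Not plausibly |
| Infant samples, arm against arm | No, as no parental reference is used |
| Primary endpoint (SCRIP score) | No |

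7. **Size.** An estimate needs three quantities: the share of swabs taken after contact, whether the swabbed site is the contact site, and how much of the swab's flora would come from the infant. The protocol gives none of them. It names no skin site, and section 7.2 does not say where the partner is swabbed.

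**The case against.** The strongest reply is that the overlap is permitted, not prescribed. The 0-6 hour window includes time zero, section 7.2 asks for prompt sampling, section 8.3 allows SSC to start late, and section 14.2 lets some infants start on the resuscitaire. A pre-contact swab fits the plan. A reader might infer that SSC-arm swabs are always taken after contact; the documents do not support that. The reply stands against that inference, but not against the point that the plan leaves the order open in one arm.

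A second reply is scope. The hypothesis in section 5.2 can be tested by comparing infant samples between arms, with no parental reference. Section 9.3 describes many outcomes as exploratory, and section 6.2 restricts some to a subsample. This stands and limits the weight of the point.

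Third, section 13.2 leaves detail to standard operating procedures, and the flow chart (section 7.3) is an appendix that is not shown. Either may fix the timing. That is possible, but the protocol's own two statements do not.

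A reader might also infer that infants held by a surrogate are compared with the wrong person. Sections 6.2 and 9.1 define the comparison as one with the parents, so for those infants it remains as defined. The surrogate is an unsampled additional contact, not an error in the endpoint.

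**Conclusion.** The concern holds in a limited form. A skin swab taken to plan may follow contact in the SSC arm but generally not in the control arm, so the skin part of the infant-parent comparison can depend on the arm. The vaginal and rectal references, the direct comparison of infant samples and the primary endpoint are unaffected.

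The conclusion assumes that SSC starts roughly as planned and that the swabbed skin is, or may be, the contact skin. Under the first assumption, five to six of the six permitted hours lie after the start of contact. It might be tempting to turn this into a bias figure by assuming a transferred fraction. The protocol supplies no such fraction, and flora moved from the infant's skin to a parent's chest need not match the fecal community on which section 6.2 defines the endpoint. No size should be claimed.

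**What to change.** Take the mother's and partner's skin swabs antenatally after consent, or at the latest before first skin contact, in the same way in both arms. Consent and background data are already collected antenatally (section 7.2), so an occasion exists. Sections 6.2 and 7.2 should give the same timing and name the skin site.

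Record the swab time and whether contact had begun. Time in SSC is already documented (sections 8.3 and 8.9), so the swab time is the main addition. Keep all swabs in the main comparison and handle post-contact swabs in a sensitivity analysis. Excluding them would remove data almost only from the SSC arm, in a way linked to rapid birth. Where a surrogate gives SSC, record it and, optionally, swab that person.

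The cost is small. Some swabs will come from parents who do not contribute an infant. Some pre-contact swabs will be missed in rapid births, or when randomisation follows birth, which section 8.6 allows for up to an hour. Tying the swab to consent and not to randomisation reduces the second loss.
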